| Study Type Hypothesis testing |
| Study Design Longitudinal cohort study |
| Feasibility counts There are approximately 5.5 million patients in England, aged 40+ and with up to standard registration for a period between 1/1/1998 to 31/12/2017 in the CPRD GOLD. Restricting to English practices (linked to HES and ONS) and only including patients fulfilling the eligibility criteria listed below, the expected population is approximately 3.3 million and out of these we expect 216,000 fall events, 230,000 myopathy/muscle pain events and 1,200 intracranial haemorrhage events. |
| Sample size considerations We have based our sample size calculation on the least common of the primary outcomes listed above (intracranial haemorrhage), and used the method developed by Riley *et al.,*^40^ to minimise the potential for overfitting and ensure precise estimates of key parameters. A sample size of approximately 80,000 patients is required for the development of a clinical prediction rule for this outcome, assuming an event rate of 24.6 per 100,000 person years,^41^ a median follow up of 7 years,^42^ a conservative estimate of Nagelkerke’s R^2^ statistic of 0.15 and a maximum number of 40 parameters per model.  Feasibility counts showed that this sample size is adequate for the development of the prediction rules. Since Intracranial bleeding is the rarest of the primary outcomes to be studied, the sample size will be sufficient for all other outcomes of interest. For validation, Vergouwe *et al.,*^43^ consider at least 100 events per sample population to be “substantial” and we will comfortably exceed this in our validation cohorts for each outcome of interest.  For analyses using causal inference methods (propensity score matching and instrumental variable analysis), assuming clinically significant increased rate of each adverse event with treatment of 10%, and an event rate of at least 0.5% per year in the non-exposed group, approximately 88,380 patients (44,190 in each group) and 4,634 events will be required to accurately define the relationship between preventative treatment and adverse events, with 90% power and an alpha of 0.05. |

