| Limitations of the study design, data sources, and analytic methods This study focuses on potential harms from adverse events associated with preventative treatments for cardiovascular disease. Such outcomes may be less well recorded in routine electronic health records. For example, initial scoping work suggests the rate of falls documented in the CPRD is between 0.06-0.34% per 1000 person-months. These incidence rates may be less than those reported in smaller previous studies (0.15-6.40% per 1000 person-months) using different definitions, captured via detailed questionnaires and follow-up.^49-52^ Incidence rates are likely to be higher when linked data from HES and ONS are available.^53^ Missing data on certain outcomes may reduce the accuracy of the prognostic models, but should not bias the results provided the data are missing at random and not affected by whether patients are prescribed treatment. To minimise the risk of reporting bias, outcomes in the primary analysis will be defined according to hospital admissions documented in the HES or ONS.  The causal inference work will use an observational cohort design, and as such, there is an inherent selection bias of patients in both exposure and control groups. The impact of this bias will be limited by propensity score methods used to control for confounding, but this approach assumes that all confounding factors are measured and accounted for within the analysis. In the present study, we will examine the validity of this assumption by 1) using an instrumental variable (GP prescriber preference) and examining the association with the outcomes of interest and 2) by studying the impact of treatment on positive and negative controls: hospitalisation and/or death from cardiovascular disease and bowel cancer/COPD. We will conclude the assumption has been met if high GP prescribers have a similar association with outcomes and the treatment itself and treatment is shown to be associated with the positive control, but not the negative control.  *Strategy for dealing with potential errors resulting from multiple testing*  This study will examine multiple outcomes across 3 exposure variables. To avoid potential errors arising from multiple testing, a primary outcome has been clearly defined for each exposure variable. Secondary outcomes are also pre-specified. The primary outcome will be given priority in the final analysis write-up and any related reports and presentations.  Primary and secondary outcomes will be defined using data from Basic inpatient HES and ONS. Sensitivity analyses will explore analyses defining these outcomes using the above sources and read-coded primary care data. The accuracy of such outcome data has been examined previously in patients with acute myocardial infarction and whilst recording of risk factor and co-morbid information was consistent across primary care, hospital admissions and disease registry records, the crude incidence of acute myocardial infarction was underestimated by up to 50% if only one data source was used, compared with using all three sources.^53^ The use of linked CPRD data will ensure outcome data are ascertained accurately. |

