| List of Appendices Appendix 1. Code lists for the primary outcomes |
| Amendments **Amendment 1 – 19/05/2019 (approved)**  **We clarify that aims 1 and 2 (prognostic model derivation and validation) of the study should include the whole population independently of whether patients are new or old users of preventative treatment; the causal inference analyses will focus on new users only:**  *L. Definition of the study population*  Patients will be excluded if they meet the following criteria:  Previous prescription of the exposure variable (antihypertensive, statin or antiplatelet; for causal inference analyses only)  **Amendment 2 – 28/06/2021 (approved 05/07/2021)**  **We have made the following revisions aimed at simplifying the analysis plan in light of the very large sample size and computational time required to conduct each analysis:** *C. Technical Summary / E. Objectives, Specific Aims and Rationale* Aims:  3) Use causal inference methods (multivariable regression, propensity score adjustment/matching, instrumental variable analysis) to examine whether modification of treatment could have an important impact on the risk of adverse events.  *L. Definition of the study population*  Study entry criteria – Patients will enter the cohort on the index date, defined as:   \| **Exposure** \| Antihypertensive therapy \| Statin therapy \| Antiplatelet therapy \| \| --- \| --- \| --- \| --- \| \| **Index date definition** \| 12 months after the first systolic blood pressure reading ≥130 mm Hg \| 12 months after the first coded or calculated CVD risk of ≥5% (equivalent to age ≥50 years for men and ≥60 years for women) \| 3 months after first CVD event \|   *N. Exposures, Outcomes and Covariates*  Positive controls are outcomes know to be affected by treatment (e.g. cardiovascular disease, death)  For causal inference analyses (only), sensitivity analyses will explore outcomes defined more broadly using primary care codes as well. *O. Data/ Statistical Analysis* We no longer plan to conduct an internal validation of the prediction models. The following text from the protocol is therefore redundant:  Where feasible and appropriate, each model will be internally validated using the bootstrap method, to allow optimism-adjusted estimates of calibration and discrimination performance to be obtained. Adjustment for overfitting will be undertaken using a uniform shrinkage factor identified from bootstrapping, followed by re-estimation of the cumulative baseline sub-distribution hazard function (and thus baseline cumulative incidence function) to maintain overall calibration between observed and predicted risks. Given the large sample size, overfitting is likely to be small (see sample size calculation above). If bootstrapping is computationally infeasible due to the large sample size, then a smaller random sample of the population will be used or alternative internal validation methods employed such as cross validation.  *Aim 3 – causal inference analysis*  For most of the outcomes described in this proposal, the association and magnitude of effect with treatment is not well defined in randomised controlled trials. We will therefore undertake causal inference work to examine whether modification of treatment could have an important impact on the risk of adverse events using two causal inference methods: multivariable adjustment, propensity score adjustment/matching and instrumental variable analysis.  For the analysis using multivariable adjustment, Cox proportional hazards models will be used to compare adverse event rates in each experimental group. Estimates will be adjusted for pre-specified variables thought to confound the relationship between treatment and adverse events.  For the analysis using propensity scores, we will conduct separate analyses adjusting for propensity score and matching via propensity score.  *Subgroup and sensitivity analyses*  Where possible and appropriate, analyses of treatment associations will be examined in subgroups of the population. These will include age, sex, baseline blood pressure and cardiovascular risk, by drug type/dose/intensity and past medical history. Subgroup definitions will be agreed by expert opinion or taken from an accompanying systematic review of previous trials, examining the same topic. For computational reasons (whereby only one imputation model is required for all subgroup analyses of each outcome), these analyses will only be undertaken using propensity score adjustment. *P. Plan for addressing confounding* Two approaches will be taken to determine whether observed associations are potentially subject to residual confounding.^46^ Where all approaches provide similar results, we can be more confident that the findings are accurate and reliable. Further steps will be taken to examine the validity of treatment effect estimates using positive and negative controls: the impact of treatment on an outcome known to be affected by treatment (e.g. cardiovascular disease and death; positive controls)  **Amendment 3 – 25.11.2021**  **We have added exploratory analyses using supervised machine learning approaches to address missing data and deal with confounding by indication in the causal inference analyses.** O. Data/ Statistical Analysis ***Aim 3 – causal inference analysis***  For most of the outcomes described in this proposal, the association and magnitude of effect with treatment is not well defined in randomised controlled trials. We will therefore undertake causal inference work to examine whether modification of treatment could have an important impact on the risk of adverse events using two causal inference methods: propensity score matching and instrumental variable analysis.  For the propensity score analysis, eligible patients will be matched 1:1 at the index date using propensity scores, which indicate the likelihood a patient will be prescribed treatment on the basis of their known (pre-treatment) characteristics and other known information which might influence the decision to treat. Predictors of preventative drug prescription will be explored in a logistic regression model. Matched patients will be compared using the Cox proportional hazards models, but hazard ratios will only be adjusted by factors unbalanced at baseline which are not already included in the propensity score model. Time since cohort entry will be used as the underlying time function in each model.  For the instrumental variable analysis, GP’s previous antihypertensive prescribing preferences will be used as an instrument to predict the likelihood of actual treatment. Risk of adverse events will be estimated in patients attending a GP considered a high prescriber of preventative medication and compared to those attending a GP considered a low prescriber. If the results from the propensity score matching suffer from unmeasured confounding, they will differ from those of the instrumental analysis. If this is the case, these models will be refined with additional factors to achieve better adjustment and matching. Where all approaches provide similar results, we can be more confident that the findings are accurate and reliable.^46^  Generative Adversarial Networks (GAN) will also be used to impute missing counterfactual data (unobserved effects of untaken treatments) on an individual level. GAN models are a class of machine learning frameworks that involves the simultaneous training of a pair of deep neural networks in competition with each other. The idea is that the first network, the generator, generates synthetic data samples that are similar to the original samples, while the second network, the discriminator, evaluates the authenticity of the generated samples [1]. Data similarity and fidelity are usually evaluated using well-known metrics such as Maximum Mean Discrepancies [2] and Jensen-Shannon Divergence [3]. While GAN’s initial uses were for imaging applications, its generative capabilities make it naturally suitable for generating missing values that can be used to impute the original samples.  In this work, we build on the intuition that treatment effects estimation and causal inference are a missing data problem, where counterfactuals (unobserved effects of untaken treatments) are missing [4]. Specifically, we plan to use GAN to impute missing counterfactual data, for the samples available in CPRD. By modifying the generator’s goal to accurately impute missing data, and the discriminator’s goal to distinguish between observed and imputed counterfactual values for the same patient record. The model can generate the missing data conditional on the observed values and assigned treatment for each patient as seen in [5, 6]. While useful, the work of [5, 6] are not compatible for time-series data nor for estimating multiple treatment effects, which limits its use in real-life treatment applications. Therefore, we plan to extend such previous works to make them compatible for multiple treatment options and for time-series data to allow for long-term treatment (antihypertensives, statins, antiplatelets) estimation effects for multi-morbid populations as initially proposed in this project.  The proposed GAN approach does not generate new patient samples, but rather generates counterfactual (missing component) conditioned on observed factual data, and outputs a complete record with both factual and counterfactual outcomes to allow for treatment effect estimation for each patient. This approach is naturally immune to re-identification attacks since no new samples are generated, but we will run privacy checks and measures within the data to verify that the model is not copying potential outcomes from patients in the training sample. Example privacy measures that we plan to apply include empirical evaluations such as mathematical privacy definitions such as identifiability [7] that quantifies the probability of re-identification to ensure that no combination of attributes could reveal the identity of a patient. Other privacy evaluation methods include testing that the model is robust against membership inference attacks, where an attacker attempts to determine if a specific patient was used in the training set of the model [8]. Lastly, we will experiment with strict theoretical guarantees such as differential privacy which allow for the model to learn almost nothing about an individual while learning useful information about a population [9].  **References**  [1] Ian Goodfellow, Jean Pouget-Abadie, Mehdi Mirza, Bing Xu, David Warde-Farley, Sherjil Ozair, Aaron Courville, and Yoshua Bengio. Generative adversarial nets. *Advances in neural information processing systems*, 27:2672–2680, 2014.  [2] Arthur Gretton, Karsten M Borgwardt, Malte J Rasch, Bernhard Sch¨olkopf, and Alexander Smola. A kernel two-sample test. *The Journal of Machine Learning Research*, 13(1):723–773, 2012.  [3] AP Majtey, PW Lamberti, and DP Prato. Jensen-shannon divergence as a measure of distinguishability between mixed quantum states. *Physical Review A*, 72(5):052310, 2005.  [4] Peng Ding and Fan Li. Causal inference: A missing data perspective. *Statistical Science*, 33(2):214– 237, 2018.  [5] Jinsung Yoon, James Jordon, and Mihaela Schaar. Gain: Missing data imputation using generative adversarial nets. In *International Conference on Machine Learning*, pages 5689–5698. PMLR, 2018.  [6] Jinsung Yoon, James Jordon, and Mihaela van der Schaar. Ganite: Estimation of individualized treatment effects using generative adversarial nets. In *International Conference on Learning Representations*, 2018.  [7] Jinsung Yoon, Lydia N Drumright, and Mihaela Van Der Schaar. Anonymization through data synthesis using generative adversarial networks (ads-gan). *IEEE journal of biomedical and health informatics*, 24(8):2378–2388, 2020.  [8] Reza Shokri, Marco Stronati, Congzheng Song, and Vitaly Shmatikov. Membership inference attacks against machine learning models. In *2017 IEEE Symposium on Security and Privacy (SP)*, pages 3–18. IEEE, 2017.  [9] Cynthia Dwork, Aaron Roth, et al. The algorithmic foundations of differential privacy. *Found. Trends Theor. Comput. Sci.*, 9(3-4):211–407, 2014.  **Amendment 4 – 30.11.2022**  **Added University of Birmingham to the list of data processors.** |

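### Amendment 3's exploratory GAN analysis aims at a treatment effect for each patient, which the data cannot identify; it can give at most an average effect given measured covariates, and only if there is no unmeasured confounding.

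*Protocol*

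**What the plan says.** Amendment 3 (section O, Aim 3) describes its additions as "exploratory analyses using supervised machine learning approaches to address missing data and deal with confounding by indication" in the causal inference analyses. After restating the propensity score and instrumental variable analyses, it says that a GAN "will also be used to impute missing counterfactual data (unobserved effects of untaken treatments) on an individual level". On what the network uses, it says: "The model can generate the missing data conditional on the observed values and assigned treatment for each patient". On what it delivers, it "outputs a complete record with both factual and counterfactual outcomes to allow for treatment effect estimation for each patient".

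The amendment states no identifying assumption for this step. On quality it makes a general remark about GANs, "Data similarity and fidelity are usually evaluated using well-known metrics such as Maximum Mean Discrepancies", and then describes privacy checks.

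The protocol's section on limitations says of the propensity score methods that "this approach assumes that all confounding factors are measured and accounted for within the analysis", and plans an instrumental variable and positive and negative control outcomes to examine this. That section does not mention the GAN.

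**The concern.** Two separate things are fixed badly.

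The first is the estimand. A patient either took the treatment or did not, and one outcome follows. The data inform the risk under treatment and the risk without it, each given covariates. They say nothing about how the two outcomes pair up within a patient. In a completed record that pairing is supplied by the network. A factual-minus-imputed difference for one patient is therefore partly a modelling artefact, however well the network reproduces the observed data.

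The second is the stated purpose. A model that conditions on recorded values and assigned treatment can balance recorded reasons for prescribing. It cannot see unrecorded ones. The protocol admits this for the propensity score and leaves it unsaid for the GAN, whose declared aim is to deal with confounding by indication.

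At stake is what the exploratory analysis may report: individual effects that the data cannot support, and an estimate that looks better protected against confounding than it is.

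**Working it through.** **Plan's own figure.** The protocol gives no performance or precision figure for the GAN, so there is none to reproduce. The illustration borrows inputs from the Aim 3 sample size paragraph, and its event count confirms how they should be read. With a hazard ratio of 1.10, two-sided alpha 0.05 and 90% power, Freedman's formula gives (2.10/0.10)² × (1.960 + 1.282)² = 4,634 events, as stated there. The 10% increase is thus a ratio of 1.10.

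**Inputs**
- Untreated rate 0.5% per year and ratio 1.10, so treated rate 0.55% per year (Sample size considerations).
- Horizon of 10 years. The protocol gives this for the Aim 1 prediction models; using it here is an assumption, as are constant rates and no competing deaths.

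**Step 1: risks.**
- Untreated: p0 = 1 − exp(−0.005 × 10) = 4.88%.
- Treated: p1 = 1 − exp(−0.0055 × 10) = 5.35%.
- Average effect: +0.47 percentage points.

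**Step 2: what the data allow for individuals.** Call a patient harmed if the event occurs only under treatment. The Fréchet bounds on the share harmed are:
- lower: max(0, p1 − p0) = 0.47%;
- upper: min(p1, 1 − p0) = 5.35%.

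The ratio is about 11. Correspondingly, the share spared an event by treatment runs from 0% to 4.88%. Every point in the range has the same two risks and the same average effect.

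**Step 3: do covariates settle it?** Take one measured binary covariate, split evenly, with no unmeasured confounding. Assume risks of 2.0% untreated and 2.2% treated at one level, and 8.0% and 8.8% at the other. The average effect is 0.5 points. Three within-patient pairings give these shares harmed:

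| Pairing | Calculation | Share harmed | Simulated (4 million patients) |
|---|---|---|---|
| As aligned as possible | (0.2% + 0.8%)/2 | 0.50% | 0.50% |
| Independent | (2.2% × 0.98 + 8.8% × 0.92)/2 | 5.13% | 5.14% |
| As opposed as possible | (2.2% + 8.8%)/2 | 5.50% | 5.50% |

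The simulated risks by covariate level and treatment agreed across the three, up to sampling error. Metrics that compare generated with observed samples cannot choose between them.

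**Step 4: unmeasured confounding.** Let the true effect be null. Let an unrecorded binary factor multiply risk by R, with prevalence q1 in treated and q0 in untreated patients. The spurious risk ratio is [1 + (R − 1)q1]/[1 + (R − 1)q0].
- R = 2, 21% versus 10.5%: 1.21/1.105 = 1.095, or about the 1.10 that the protocol calls clinically significant. A simulation gave 1.10 at both levels of the measured covariate.
- R = 1.5, 20% versus 10%: 1.10/1.05 = 1.05.
- R = 3, 30% versus 15%: 1.60/1.30 = 1.23.

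All values of R, q1 and q0 are assumptions. A GAN conditioned on the measured covariates would reproduce this bias, as a propensity score would.

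**The case against.** The best defence is that the analysis is labelled exploratory and runs beside the propensity score and instrumental variable analyses. It replaces neither. Adjusting for recorded indications is a legitimate way of dealing with confounding by indication, and the amendment nowhere claims to remove unmeasured confounding. The sections on outcomes and on confounding plan positive and negative controls for treatment effect estimates in general, so the check arguably covers the GAN already. The range in Step 2 also concerns a quantity that the protocol does not propose to report, and it shows no error in an average effect. All of this stands and limits the weight of the point. It does not rescue the stated target: the text speaks of imputation at individual level and of an effect per patient. If conditional averages are meant, the protocol should say so.

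Three stronger readings are tempting and are not supported.
- A reader might infer that individual counterfactuals will feed the planned risk calculator. The rationale ties that tool to the prediction models, the dissemination section speaks only generally of the results, and nothing sends GAN output there.
- A reader might infer that agreement between the GAN and the propensity score already counts as confirmation. The sentence on similar results closes the paragraph on the propensity score and the instrument, before the GAN is introduced.
- A reader might infer that completed records will be analysed as if fully observed, giving standard errors that are too small. The protocol states no variance method for the GAN, so no size can be put on this.

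**Conclusion.** The point holds as a defect in how an exploratory analysis is defined. The per-patient effect is not identified. What can be estimated is the average effect given measured covariates, and that requires no unmeasured confounding, overlap between treatment groups and a well-defined treatment. The first conclusion follows from the design and needs no numerical assumption. The roughly 11-fold range (about 0.5% to 5.4% harmed) only illustrates it and rests on the protocol's planning rates and an assumed 10-year horizon. The spurious ratios of 1.05 to 1.23 rest wholly on assumed confounder strengths and show what could happen, not what will. The propensity score and instrumental variable results are untouched. The change is worth making because it alters what the GAN analysis may report.

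**What to change.** Amend the GAN text as follows.
- Define the estimand as the average treatment effect given covariates, and report no factual-minus-imputed effect for an individual.
- Give uncertainty that reflects both imputation and network training, from repeated refits or multiple draws.
- State that the method assumes no unmeasured confounding, and limit the claim about confounding by indication to measured factors.
- State that the positive and negative controls already planned also apply to the GAN estimates.
- State that agreement between the GAN and the propensity score is not independent evidence against unmeasured confounding.

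Most of this is wording. The real cost is computing time for the repeated training runs.
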